**Inclusion and exclusion criteria.**

Study will recruit all patients that have a history of snake bite and randomize all patients that then receive antivenom. The exclusion criteria will be

- Age < 14 years
- Pregnancy
- Previous administration of antivenom

All appropriate methods have been used to avoid bias:

1. Randomization method is independent of the investigators and dependent on a computer algorithm;
2. Treatment allocation cannot be predicted in advance
3. The primary and secondary outcomes are objective measures
4. All outcomes will be recorded prospectively by the study team and not by the treating doctors
5. Patient follow-up will be complete
6. Analysis will be by intention to treat.

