**Research Plan:**

**Study centre**: Base Hospital Chilaw, Anuradhapura, Peradeniya for a period of 12 months. It is an original study, **A randomized, open label, controlled clinical trial.** A total 240 patients will be recruited in this study.

A randomized, double-blind, controlled clinical trial with two parallel groups:

- 10 vials of polyvalent antivenom administered in Normal saline (500ml) over 20 minutes*
- 10 vials of polyvalent antivenom administered in Normal saline (500ml) over 2 hours*

If the patient is administered more than 10 vials then this will be given at the same rate =10 vials over 20 minutes or 2 hours (Although the volume and dilution can be modified for convenience).For example 20 vials given over 40 minutes in 500 ml of Normal saline.

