| **I**  Mild(skin and subcutaneous tissues only) | Generalized erythema,urticaria, periorbital oedema or angioedema. |
| **2**  Moderate(features suggesting respiratory, cardiovascular, or gastrointestinal involvement) | Dysponea,stridor,wheeze,nausea,vomiting,  dizziness (pre syncope) diaphoresis, chest or throat tightness or abdominal pain. |
| **3**  Severe (hypoxia, hypotension or neurological compromise) | Cyanosis or SpO2 less than or equal 92% at any stage, hypotension,(SBP<90mmHg in adults)confusion, collapse, LOC or incontinence. |

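### The protocol lists objective outcomes as a bias safeguard, but the Brown-graded outcomes partly rest on judged signs and reported symptoms that nothing described would mask from the arm.

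*Protocol*

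**What the plan says.** The list of bias safeguards under Inclusion and exclusion criteria states at item 3, without restriction, that "The primary and secondary outcomes are objective measures". Item 4 adds that "All outcomes will be recorded prospectively by the study team and not by the treating doctors".

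The section Description of all medical procedures and safety measures defines the primary outcome as Brown grade 3 within 4 hours of starting antivenom. The grading table there gives two measured thresholds for grade 3 (SpO2 at or below 92%, systolic pressure below 90 mmHg). It also lists cyanosis and "confusion, collapse, LOC or incontinence", any of which appears to qualify. Grade 1 is made of skin signs. Grade 2 includes respiratory signs, nausea and vomiting, and "dizziness (pre syncope) diaphoresis, chest or throat tightness or abdominal pain". Grades 1 and 2 form a secondary outcome. The other secondary outcomes include elevated mast cell tryptase and elevated complement, which are laboratory assays.

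On masking, the Research Plan says "A randomized, open label, controlled clinical trial" and then "A randomized, double-blind, controlled clinical trial with two parallel groups". The arms are "10 vials of polyvalent antivenom administered in Normal saline (500ml) over 20 minutes" and "10 vials of polyvalent antivenom administered in Normal saline (500ml) over 2 hours". No dummy infusion is described, and the paper in each randomisation envelope names the infusion time in plain words.

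**The concern.** Item 3 is the only listed safeguard that speaks to how outcomes are scored. Item 4 separates the recorder from the treating doctor, but a study team member at the bedside can still see how fast the bag is running. The patient who reports dizziness or tightness can see it too.

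The expectation also runs one way. The Background reports general expert agreement that rapid administration provokes early reactions, and the main hypothesis is that slow infusion is safer. If borderline confusion or cyanosis is called a severe reaction more readily in the fast arm, part of the recorded difference comes from scoring. The opposite tendency would hide part of a true effect. A reader who relies on item 3 would not look for either.

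**Working it through.** **Step 1. The plan's own sample size.** Inputs from the sample-size section: 50% versus 30%, alpha 5% (taken as two-sided), power 80%.

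- Uncorrected: n = [1.960·√(2·0.4·0.6) + 0.8416·√(0.5·0.5 + 0.3·0.7)]² / 0.2² = (1.358 + 0.571)² / 0.04 ≈ 93.0.
- With continuity correction: (93.0/4)·[1 + √(1 + 4/(93.0·0.2))]² ≈ 102.8, so 103 per arm.

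This matches the stated 103, so the sample-size arithmetic is not at issue. The recruitment target of 240 gives 120 per arm.

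**Step 2. Which outcomes item 3 describes correctly.**

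| Outcome | Basis in the protocol | Does the objectivity claim hold? |
|---|---|---|
| Grade 3 (primary) | SBP and SpO2 thresholds, or cyanosis, confusion, collapse, LOC, incontinence | In part |
| Grades 1 and 2 (secondary) | Skin signs, examiner findings, reported symptoms | No |
| Tryptase, complement (secondary) | Laboratory assay | Yes |

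**Step 3. False positives from one-sided over-calling.** The documents give no over-call rate, so a range f = 2%, 5%, 10% is assumed. With true risk p in both arms, the recorded rates are p in the slow arm and p + (1 − p)·f in the fast arm. The rejection probability is the sum over all pairs (x, y) of Bin(x; 120, fast)·Bin(y; 120, slow), counted where X² = 240·[x(120 − y) − y(120 − x)]² / [120·120·(x + y)(240 − x − y)] exceeds 3.84 (uncorrected chi-squared).

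| True risk p | f | Recorded fast-arm rate | Extra events among 120 | Chance of a significant result |
|---|---|---|---|---|
| 50% | 2% | 51.0% | 1.2 | 4.8% |
| 50% | 5% | 52.5% | 3.0 | 6.2% |
| 50% | 10% | 55.0% | 6.0 | 11.4% |
| 30% | 2% | 31.4% | 1.7 | 5.6% |
| 30% | 5% | 33.5% | 4.2 | 8.9% |
| 30% | 10% | 37.0% | 8.4 | 20.8% |

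The 50% is the planned fast-arm rate. The lower rate is shown because the sample-size section ties the 50% to grade 2 or 3 reactions, while the primary outcome is grade 3 alone.

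**Step 4. The opposite direction.** With true risks of 50% and 30%, over-calling 5% or 10% of slow-arm non-events lifts the recorded slow-arm rate to 0.3 + 0.7·0.05 = 33.5% or 0.3 + 0.7·0.10 = 37.0%. By the same enumeration, power falls from 89% to 74% or 53%.

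**The case against.** The strongest reply is that the primary outcome is mostly protected. Two of its criteria are instrument readings; loss of consciousness, collapse and incontinence are gross events; and every reported symptom sits in grade 2. The sample-size section says earlier grade 2 or 3 reactions were most commonly hypotension, so grade 3 calls that rest only on a judged sign should be a minority. This stands, and it limits the point. At a 2% over-call the error rate stays close to 5%.

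A reader might infer that no outcome is objective, or that only blood pressure and SpO2 are. The documents do not support that: tryptase and complement are assays. Length of stay can also be recorded without grading. Clinicians who know the arm may influence it, but that concerns care, not scoring.

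It can also be said that the protocol calls itself double-blind. It does, in the same section that calls it open label, and nothing described would deliver masking.

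Finally, a supportive analysis on the measured criteria may belong in a statistical analysis plan that is not shown. Its absence here is therefore no fault. The fault is the unrestricted statement in item 3, together with two incompatible masking statements.

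**Conclusion.** The point holds for the Brown-graded outcomes. Item 3 claims a safeguard that the design has only in part: partial exposure for grade 3, greatest exposure for grades 1 and 2, none from bedside grading for tryptase and complement.

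The size depends on over-call rates that the documents do not give. With 5% of fast-arm non-events over-called, the error rate is 6.2% at a 50% risk and 8.9% at 30%; with 10%, it is 11.4% and 20.8%. These figures assume 120 per arm, no true difference, errors in one arm only, and an uncorrected two-sided test.

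A reader might go further and infer that a real effect could never be told from a scoring effect. That goes too far: most events may rest on a blood pressure reading, and the components can be separated if they are charted.

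**What to change.** 1. Reconcile the Research Plan to one masking statement. Open label is the one that fits the design described. Limit item 3 to the SBP and SpO2 criteria and the laboratory outcomes, and state that the sign- and symptom-based Brown criteria are recorded unmasked.
2. Chart each Brown component with its time, and derive the grade from the chart by a fixed rule instead of an overall bedside impression.
3. Beside the primary result, report grade 3 by instrument criteria only: SBP below 90 mmHg or SpO2 at or below 92% at the scheduled readings. Restricting it to scheduled readings keeps extra readings prompted by knowledge of the arm from adding events. Use the same test, absolute risk reduction and 95% confidence interval. State that a difference seen only in the judged signs will be interpreted with caution.

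The cost is protocol wording, a tick-box form and a short program, with no extra staff, visits or procedures. The supportive analysis will have fewer events and somewhat wider intervals. It will miss events between scheduled readings, and these are hourly after the first hour, when the 2-hour infusion is still running, so it should not replace the primary analysis. Bias in signs ticked by unmasked staff is exposed by these steps, not removed.

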**Description of all medical procedures and safety measures**

All eligible patients will have baseline clinical data collected, including clinical symptoms, signs and a whole blood clotting test (WBCT). Baseline blood will be collected (see below).

Patients in the first treatment group will receive 10 vials of antivenom in 500 ml of normal saline over 20 minutes. Patients in the second treatment group will receive 10 vials of antivenom in 500 ml of normal saline over 2 hrs. Patients will be closely observed for the four hour period following the commencement of administration of antivenom. The patient will be put on a cardiac monitor for this period if possible. For the first hour, HR, BP, RR, oxygen saturation and temperature will be measured every 5 minutes and hourly for the remainder of the four hours. Patients will be observed for evidence of an allergic reaction using the Brown grading system, including auscultation of the chest. Allergic reactions will be treated as per the current protocol of antivenom reactions with intravenous fluids and adrenaline.

A 15 ml sample of blood will be taken using a sterile technique (syringe and needle) from each patient consenting to the study. Normal coagulation studies will be performed on samples for patients who developed coagulopathy. Creatine kinase will be measured in patients with Russell’s viper bite. Serial mast cell tryptase, complement and anaphylactic mediators will be measured in all patients who receive antivenom by the laboratory of Assoc. [name] in Western Australia. Urine will be collected in patients with Russell’s viper bite.

Throughout the trial, the patient will remain under the responsibility of the admitting consultant. Both study and host hospital clinicians will report to this individual.

**Primary outcome:** proportion with severe systemic allergic reactions (grade 3 by Brown grading system) within 4 hours of commencement of antivenom.

**Secondary outcomes:** proportion with elevated mast cell tryptase: proportion with elevated complement; hospital length of stay; proportion with mild and moderate allergic reaction (grade 1 and 2 Brown grading); and proportion with delayed administration of further antivenom therapy. Proportion developing serum sickness will be determined in a smaller number because follow up after discharge is difficult in the rural hospital setting.

Brown Grading System for systemic allergic reactions.

| Grade | Clinical Effects |
| --- | --- |
| **I**  Mild(skin and subcutaneous tissues only) | Generalized erythema,urticaria, periorbital oedema or angioedema. |
| **2**  Moderate(features suggesting respiratory, cardiovascular, or gastrointestinal involvement) | Dysponea,stridor,wheeze,nausea,vomiting,  dizziness (pre syncope) diaphoresis, chest or throat tightness or abdominal pain. |
| **3**  Severe (hypoxia, hypotension or neurological compromise) | Cyanosis or SpO2 less than or equal 92% at any stage, hypotension,(SBP<90mmHg in adults)confusion, collapse, LOC or incontinence. |

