**ii. Detailed description of the research method.**

All patients bitten by a snake will be eligible for the study and will be approached at the time of admission, however they will not formally enter the interventional trial until the decision is made to administer antivenom. All eligible patients will have baseline clinical data collected, including clinical symptoms, signs and a 20 minute whole blood clotting test (20 WBCT). Baseline blood will be collected (see below). When a decision to administer antivenom is made, the patient will be randomized to one of the two parallel treatment arms. Patients in the first treatment group will receive 10 vials of antivenom in 500 ml of normal saline over 20 minutes [alternatively 20 vials of antivenom in 500 ml of normal saline over 40 minutes] Patients in the second treatment group will receive 10 vials of antivenom in 500 ml of normal saline over 2 hrs [alternatively 20 ampoules of antivenom in 500 ml over 4 hours.]

Randomisation will be done by computer in blocks of four (eg. AABB, ABAB etc.) using Microsoft Excel. The computer generated list will be used to randomize pieces of papers to sequentially ordered envelopes with the wording “20 minute infusion” or “2 hour infusion”

Patients will be closely observed for the four hour period following the commencement of administration of antivenom. The patient will be put on a cardiac monitor for this period if possible. For the first hour, HR, BP, RR, oxygen saturation and temperature will be measured every 5 minutes and then every hour for the remainder of the four hours. Patients will be observed for evidence of an allergic reaction using the Brown grading system,(10) including auscultation of the chest. Allergic reactions will be treated as per the current protocol of antivenom reactions with intravenous fluids and 0.5 mg of intramuscular adrenaline into the lateral thigh (or upper arm if not possible).

A 15 mL sample of blood will be taken using a sterile technique (syringe and needle) from each patient.

- 1. The 15mL sample will be divided between one serum (red top tube), one EDTA tube (purple top) and one plasma citrate (blue top) tube.
  2. The serum tube will be spun and the serum aliquoted into 3 portions and frozen.
  3. The citrate plasma tube will be immediately double spun and then aliquoted into two separate tubes and immediately frozen.
  4. The EDTA tube will be spun and aliquoted into two separate containers.

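### The primary outcome window closes 4 hours after the start of antivenom, which is when a 20-vial slow infusion ends, so late slow-arm reactions can be scored as prevented

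*Protocol*

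**What the plan says.** The primary outcome, in the Protocol section Description of all medical procedures and safety measures, is the proportion of patients with a Brown grade 3 reaction "within 4 hours of commencement of antivenom". Study observation uses the same clock. Section ii, Detailed description of the research method, states: "Patients will be closely observed for the four hour period following the commencement of administration of antivenom".

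The Research Plan sets the two arms as "10 vials of polyvalent antivenom administered in Normal saline (500ml) over 20 minutes" and "10 vials of polyvalent antivenom administered in Normal saline (500ml) over 2 hours". For larger doses it adds: "If the patient is administered more than 10 vials then this will be given at the same rate". Section ii spells out the 20-vial case, with "alternatively 20 vials of antivenom in 500 ml of normal saline over 40 minutes" in the fast arm and "alternatively 20 ampoules of antivenom in 500 ml over 4 hours" in the slow arm.

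Nothing in the protocol ties the outcome window or the acute observation period to the end of the infusion, or lengthens either for a larger dose.

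**The concern.** The randomised factor is the length of the infusion. With a window fixed from the start of treatment, that factor also decides how much time after the dose is observed. If slow infusion delays some reactions without preventing them, those that fall after 4 hours count as non-events, while the same reactions in the fast arm fall inside the window. The error runs in the direction of the main hypothesis, that slower infusion reduces severe reactions.

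The Background says the answer will guide practice, and that rapid administration is often important in severe envenoming. A benefit of slow infusion that came partly from the cut-off would therefore matter. Neither planned analysis repairs it. Intention-to-treat keeps patients in their arms but does not recover unobserved events. A log-rank test that counts time from the start of antivenom and stops at 4 hours has the same cut-off.

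**Working it through.** **Plan's own figure.** For 50% against 30%, two-sided alpha 5% and power 80%, the usual two-proportion formula gives

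n = [1.96·√(2·0.4·0.6) + 0.842·√(0.25 + 0.21)]² / 0.2² = 93 per arm.

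The continuity correction, (n/4)·[1 + √(1 + 4/(0.2·n))]², raises this to 102.8, so 103 per arm. The protocol's 103 (206 in total) is reproduced. It does not involve the window, so a changed window with the same assumed rates leaves it as it is.

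**Step 1. Time after the infusion inside the window (no assumptions).** This is 240 min minus the infusion time. Infusion times come from the Research Plan and section ii; the 30-vial row only extends the same-rate rule.

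| Dose | Fast: infusion / left | Slow: infusion / left |
| --- | --- | --- |
| 10 vials | 20 / 220 min | 120 / 120 min |
| 20 vials | 40 / 200 min | 240 / 0 min |
| 30 vials | 60 / 180 min | 360 / window closes 120 min before the end |

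**Step 2. Illustration of size (assumptions not in the protocol).** Suppose the trigger is uniform over an infusion of T minutes, the lag from trigger to reaction is exponential with mean L minutes, and the window is W minutes. The share of reactions inside the window, for T no longer than W, is

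captured = 1 − (L/T)·[exp(−(W − T)/L) − exp(−W/L)].

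Example with 20 vials, slow, L = 60, W = 240: 1 − 0.25·(1 − exp(−4)) = 75.5%. The false difference is 0.5 × (captured fast − captured slow), with a true risk of 50% in both arms.

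| Mean lag | 20 vials: fast / slow captured | False difference | 10 vials: fast / slow captured | False difference |
| --- | --- | --- | --- | --- |
| 15 min | 100% / 93.8% | 3.1 points | 100% / 100% | 0.0 points |
| 30 min | 99.9% / 87.5% | 6.2 points | 100% / 99.6% | 0.2 points |
| 60 min | 97.4% / 75.5% | 11.0 points | 97.8% / 94.1% | 1.8 points |

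**Step 3. Whole trial.** If a quarter of patients receive 20 vials (an assumption) and the rest 10:

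- L = 15: 0.25·3.1 + 0.75·0.0 = 0.8 points
- L = 30: 0.25·6.2 + 0.75·0.2 = 1.7 points
- L = 60: 0.25·11.0 + 0.75·1.8 = 4.1 points

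**Step 4. Effect on the test.** Let f be the share given 20 vials and m the share of slow-arm 20-vial reactions that fall after 4 hours, with no other losses. The false difference is 0.5·f·m. With 120 per arm and the two-sided pooled z test (equivalent to chi-squared):

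- f = 0.25, m = 0.10: 1.25 points, type I error 5.4%
- f = 0.5, m = 0.2: 5 points, type I error 12.1%
- f = 1, m = 0.2: 10 points, type I error 34.3%

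**Step 5. What a longer common window does.** Take W as the slow-arm infusion time for the dose plus a period P. For 20 vials and L = 60, P = 120 min (W = 360) captures 99.6% fast and 96.7% slow, leaving 1.5 points. P = 240 min (W = 480) captures 100.0% and 99.6%, leaving 0.2 points.

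**The case against.** A single clock from the start of treatment is a conventional window and does not depend on allocation. The main hypothesis is stated for 10 vials, and the section that defines the primary outcome describes only 10-vial regimens. There the window covers the whole slow infusion and 2 hours beyond it. Twenty vials appears as a bracketed alternative of unstated frequency. The Background speaks of early complement-mediated reactions after rapid administration; if triggering clusters soon after the start in both arms, little is lost at 4 hours. A longer window also has a price: hypotension, hypoxia, confusion or collapse in an envenomed patient need not be allergic, so it may admit a few more non-allergic events.

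Much of this stands, and it limits the size. It does not remove the imbalance in step 1, which follows from the protocol's own durations and is not corrected anywhere.

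It also rules out several stronger readings that a reader might infer:

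- **Losses fall almost only in the slow arm.** Not at 10 vials: with a 60-minute lag, about 2.2% of fast-arm and 5.9% of slow-arm reactions are missed. Even at 20 vials, only reactions with onset after 4 hours are lost.
- **The bias is 6 to 11 points for the trial.** Those figures belong to 20-vial patients alone and leave out the 15-minute lag, which gives about 3.
- **Part of a very large dose is given unobserved.** No dose above 20 vials is named. What ends at 4 hours is scheduled study observation; the patient remains under the admitting consultant.
- **A false dose-by-arm interaction is certain.** The planned analysis by initial dose could be distorted, but that depends on the same unknown onset times.

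**Conclusion.** The point holds in limited form. It is certain that the window gives the slow arm less time after the infusion (0 against 200 minutes at 20 vials, 120 against 220 at 10), and that nothing in the protocol offsets this. The direction, in favour of slow infusion, is well supported if reactions occur during or soon after the infusion.

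The size is not known. Under the illustrative model the false difference is about 3, 6 and 11 points among 20-vial patients for mean lags of 15, 30 and 60 minutes, 0 to 2 points among 10-vial patients, and roughly 1 to 4 points overall if a quarter receive 20 vials. These figures rest on a uniform trigger, an exponential lag and a true risk of 50% in both arms, and they shrink in proportion if the true grade 3 risk is lower. The documents do not support the claim that the trial's result would be decided by this. They do support correcting it before recruitment, since reactions that nobody recorded after 4 hours cannot be recovered reliably later.

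**What to change.** Reconcile the outcome window with the permitted infusion durations:

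1. Define one primary window, identical in both arms: from the start of antivenom to the scheduled end of the slow-arm infusion for the dose ordered, plus a fixed post-infusion period stated in the protocol. A single window based on the longest permitted infusion plus that period would also do, and avoids a window that differs by dose.
2. If the window depends on dose, record the ordered dose before the envelope is opened, so that its length cannot depend on allocation.
3. Continue scheduled study observation, in both arms, to the end of the window.
4. Keep the 4-hour proportion as a secondary or sensitivity result.

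The cost is a protocol amendment to the outcome definition and a few more hours of observation by a team that the protocol already places in the hospitals around the clock, with possibly a few more non-allergic grade 3 events. A dose-specific window also needs care in the analysis by initial dose. The sample size formula, the doses and the infusion rates are unaffected.

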**Objectives:**

General Objective

To determine, whether slowing the rate of antivenom infusion will reduce the frequency and severity of antivenom reactions in patients with snake envenoming.

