**How the sample size was determined:**

In two previous studies approximately 50% of patients administered antivenom had a Brown grade 2 or 3 systemic allergic reaction (most commonly hypotension). (4,8) A reduction (absolute) of 20% would be clinically significant and would be sufficient to warrant the use of premedication. In order to detect whether premedication reduces the rate of allergic reactions from 50% to 30%, with a significant level (alpha) of 5% and a power of 80%, a minimum of 103 patients must be recruited to each arm of the trial (i.e. A total of 206 patients). To ensure appropriate recruitment and loss of patients the aim will be to recruit 240 patients.

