**iii. Description of data analysis procedure**

The RCT aims to determine the effectiveness of two different infusion rates of antivenom administration. The primary analysis will be done by intention-to-treat using the chi squared test for the primary outcome (or Fisher’s exact test if appropriate) and for other dichotomous outcomes. The relative risk (and risk reduction)and absolute risk reduction (with 95% confidence intervals) will also be calculated. For the outcomes (mainly the primary outcome) where the time –to-event is recorded, the log rank test will be used to compare treatment groups.

Analysis of trends in treatment effect for factors ‘initial dose of antivenom’ and ‘use of antivenom prior to hospital admission’ will also be performed using statistical modeling techniques.

Admission blood samples will be retrospectively analysed to confirm the identity of the snake. The primary analysis will then be repeated to correct for this.

The main hypothesis is that a slower infusion rate of antivenom (10 vials over 2 hours versus 20 minutes) will reduce the rate of all severe allergic reactions following antivenom administration from 50% to 30%.

We also want to determine if the severity of antivenom reaction is inversely related to the severity of envenoming. This will be done by comparing the concentration of venom in patient’s blood (ELISA) to severity of reaction for individual snake species.

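### The grade 1–2 secondary outcome has no interpretable direction beside a grade 3 primary, and no listed outcome measures how often any reaction occurs

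*Protocol*

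**What the plan says.** The Protocol's Objectives section asks whether slowing the infusion "will reduce the frequency and severity of antivenom reactions in patients with snake envenoming". So both frequency and severity are in scope.

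Under Description of all medical procedures and safety measures, the primary outcome is the "proportion with severe systemic allergic reactions (grade 3 by Brown grading system) within 4 hours of commencement of antivenom". One of the secondary outcomes is the "proportion with mild and moderate allergic reaction (grade 1 and 2 Brown grading"). The grading table that follows presents the grades as separate levels; grade 1, for instance, is headed "Mild(skin and subcutaneous tissues only").

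The section Description of data analysis procedure applies the chi-squared test (or Fisher's exact test) to the primary outcome and "for other dichotomous outcomes", with relative risk and absolute risk reduction also to be calculated. Its main hypothesis is that slower infusion "will reduce the rate of all severe allergic reactions following antivenom administration from 50% to 30" per cent.

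No outcome is listed for a reaction of any grade, for grade 2 or higher, or for the grade treated as an ordered scale. The protocol does not state that each patient is classified by worst grade, or that grade 3 patients are left out of the secondary.

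**The concern.** If each patient is counted once, at the worst grade, the primary and this secondary divide the reacting patients between them. A patient whose reaction is grade 2 instead of grade 3 because the infusion was slow leaves the primary and enters the secondary. The protocol counts lower severity as success, so this movement is an intended effect. Yet it pushes the secondary in the direction that a risk reduction would label as harm.

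Prevention of mild reactions pushes the same outcome the other way. A rise, a fall or no change can therefore each accompany a real benefit, and a chi-squared test with a relative risk cannot separate the two movements. The outcome measures neither the frequency of reactions nor their severity, so the frequency half of the objective has no matching clinical outcome.

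**Working it through.** **The plan's own figure.** Inputs from How the sample size was determined: 50% against 30%, "with a significant level (alpha) of 5% and a power of 80" per cent, and "a minimum of 103 patients must be recruited to each arm of the trial". Two-sided, pooled variance under the null:

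n = [1.960·√(2·0.40·0.60) + 0.8416·√(0.50·0.50 + 0.30·0.70)]² / 0.20² = (1.3579 + 0.5708)² / 0.04 = 93.0

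With continuity correction: (93.0/4)·[1 + √(1 + 4/(93.0·0.20))]² = 102.8, that is 103 per arm. The stated size reproduces, and 103 is used below.

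**Assumptions not in the protocol.** In the rapid arm 25% have no reaction, 25% have grade 1–2 as worst grade, and 50% have grade 3. Grade 3 falls to 30% in the slow arm. A share f of those 20 points moves to grade 1–2 and the rest to no reaction, so slow-arm grade 1–2 is 25% + 20%·f (net of any mild reactions prevented).

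**Chance of a significant rise in grade 1–2 with slow infusion** (uncorrected two-sided 5% test, rise only):

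Φ{[(p₂ − p₁) − 1.960·√(2p̄(1−p̄)/n)] / √[(p₁(1−p₁) + p₂(1−p₂))/n]}

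- f = 1, 25% vs 45%: (0.200 − 1.960·0.0665)/0.0650 = 1.07, giving 86%. Any reaction is 75% in both arms.
- f = ½, 25% vs 35%: (0.100 − 1.960·0.0639)/0.0635 = −0.40, giving 35%. Any reaction is 75% vs 65%.
- f = ¼, 25% vs 30%: (0.050 − 1.960·0.0622)/0.0621 = −1.16, giving 12%. Any reaction is 75% vs 60%.
- f = 0, 25% vs 25%: 2.5%, the nominal rate.

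In the first case the rounded expected counts are 26/103 vs 46/103, with p = 0.0035 (0.0055 with continuity correction), although severe reactions fell by 20 points and no patient was made worse.

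**Proportional odds.** The odds ratio is (0.30/0.70)/(0.50/0.50) = 0.429. The odds of any reaction go from 0.75/0.25 = 3 to 3·0.429 = 1.286, that is 56.25%. Slow-arm grade 1–2 is 56.25% − 30% = 26.25%. The same formula gives significant apparent harm in about 4% of trials and significant benefit in about 2% (1.5%). Any reaction, 75% vs 56.25%, shows the benefit in about 81%. Depending on rounding and method of calculation, the harm figure is 3–4% and the any-reaction figure 81–83%.

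**Lower grade 3 rates.** The 50% is given for grade 2 or 3 in the sample size section and for severe reactions in the main hypothesis, so the grade 3 rate may be lower. With full downgrading and 25% grade 1–2 in the rapid arm:

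- Grade 3 from 20% to 10% (grade 1–2 from 25% to 35%): 35%.
- Grade 3 from 20% to 12% (25% to 33%): about 25%.
- Grade 3 from 10% to 6% (25% to 29%): about 9%.

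**The case against.** Four points deserve weight.

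First, exclusivity is inferred. The text could mean one proportion per grade, or patients with mild or moderate features whatever else occurred. If grade 3 patients were also counted, the problem would shrink. This stands as a limit: worst grade is the natural reading, but a reader should not take it as something that the protocol states.

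Second, the 86% needs every averted severe reaction to become milder and no net prevention of reactions, although the objective expects frequency to fall as well. This also stands. If slow-arm grade 1–2 fell to 15%, there would be practically no apparent harm, and significant benefit in about 43% of trials. The 86% is the top of a range. The objection does not rescue the outcome, however: under proportional odds it hardly moves, and it misses a benefit that any reaction would usually show.

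Third, the secondary will be read beside the primary. In the full-downgrading case about 90% of trials with a significant rise in grade 1–2 also show a significant fall in grade 3, and with half downgraded about 96% do. A reader might infer from this concern that the trial would conclude that slow infusion is harmful. The documents do not support that, because the main hypothesis rests on severe reactions alone. What remains is a secondary that has to be decoded with the primary before it means anything.

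Fourth, adding the two proportions recovers any reaction, and an analysis plan could present it. That is true on the worst-grade reading, but the outcome is defined in the protocol, and its planned test and risk reduction apply to the exclusive category.

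**Conclusion.** The point holds as a weakness in the definition of one secondary outcome. Read naturally, the grade 1–2 proportion moves up or down according to the balance of downgrading and prevention, so its direction cannot be interpreted. The frequency of any reaction, half of the stated objective, has no outcome of its own.

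With grade 3 falling from 50% to 30%, the chance of significant apparent harm runs from practically nil, where mild reactions are prevented in number, to about 86% with full downgrading. With lower grade 3 rates (20% falling to 10–12%) and full downgrading it is about 25–35%. All these figures rest on the worst-grade reading and on an assumed 25% grade 1–2 rate in the rapid arm. The protocol gives neither that rate nor the share downgraded. The protocol's two descriptions of the 50% also conflict: if 50% covers grades 2 and 3 together, a 50% grade 3 rate leaves no grade 2 reactions at all.

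The primary conclusion, the reproduced 103 per arm and the data collection are untouched.

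**What to change.** Replace this secondary with two cumulative proportions, each by worst grade within 4 hours of starting antivenom: any reaction (grade 1 or higher) and moderate or severe reaction (grade 2 or higher). State that each patient is classified once, by worst grade. Show the separate grades 0 to 3 by arm in a descriptive table without a test. An ordinal comparison of worst grade (proportional odds model or Wilcoxon rank-sum test) is optional.

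Under pure downgrading the cumulative proportions can only stay level or fall, so apparent harm occurs at no more than the nominal 2.5%. They do not guarantee power: any reaction at 75% vs 65% reaches significance in only about 35% of trials with 103 per arm.

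The cost is a change of wording and one more analysis, using grades that are already to be recorded. No extra patients, visits or samples are needed.
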